**Figure 4 figure4:**
[figure not shown]
Smartphone App Design: Dashed lines indicate app components available based on timing (Daily and Weekly Check-Ins) or completion of other components (Daily Review, Review Something Else). EWS: early warning signs; MSS: manage signs and symptoms; PHQ: Patient Health Questionnaire 8; AMRS: Altman Mania Rating Scale; i: Instructions; gear symbol: settings.

Monitoring is a major determinant of behavior change [58], an essential strategy for empirically supported bipolar disorder psychotherapies [11,18,97,99], and individuals with bipolar disorder are interested in using self-monitoring tools [32,33]. Thus, the core of the app is a Daily Check-In (Figure 3). The Daily Check-In monitors medication adherence, sleep duration, routine (bedtime and risetime), and wellness level. These targets were selected for daily monitoring because they are consistently addressed in the core content of adjunctive psychotherapy interventions [5,18,26,33,97,98,137] and are readily amenable to goal setting and self-monitoring. Users were asked to check-in daily for 16 weeks. On the basis of data from the Daily Check-In, the Daily Review uses an expert system to provide adaptive, personalized real-time feedback [64]. As described in detail elsewhere [64], the rules linking delivery of feedback and the Daily Check-In data were developed based on existing literature regarding bipolar disorder and psychiatrist feedback from a web-based survey. This feedback reinforces success and directs users to relevant app sections (within Foundations, Toolbox, and Wellness Plan) to assist users with making adjustments if needed (Figures 3 and 4). If the Daily Check-In data indicate a need for additional clinical support based on the expert system algorithms [64], users receive feedback to contact their psychiatrist, and a message with a link to the psychiatrist’s phone number appears. An example of opening the app and completing a Daily Check-In followed by a truncated example of Daily Review feedback is displayed in Figure 5, and a more detailed use case scenario is provided in Multimedia Appendix 3.

**Figure 5 figure5:**
[figure not shown]
Daily Check-In and Daily Review: (A) Upon opening the LiveWell app, user views the home page with Daily Check-In highlighted indicating task to be completed, (B) User completes Daily Check-In with a wellness rating of -2 indicating possible early warning signs of depression, (C) After user submits Daily Check-In data, Daily Review feedback page displays summary of last 7 check-ins. Expert system identifies a possible shift in mood down as priority, (D-E) User continues through Daily Review and receives information about Awareness and Action, F. Last page of Daily Review suggests user check My Skills in Resources in the Wellness Plan. Daily Review feedback truncated here for display.

Users also complete a Weekly Check-In, including the 8-question Patient Health Questionnaire (PHQ-8) [138], Altman Self-Rating Mania Scale (ASRM) [139], and checklists for early warning signs of depression and mania [140-142]. Users receive feedback and a pop-up message if their Weekly Check-In responses indicate the new onset of an episode. For example, if the PHQ-8 score transitions from <10 to ≥10, suggesting the onset of a depressive episode based on the published threshold [138], the pop-up message says, “Looks like you may be entering a depressive episode. Call your psychiatrist to check-in.” and contains a link to the psychiatrist’s phone number to prompt a call [64]. Overall, the app content encourages users to work with a psychiatrist to come to a mutual understanding of clinical problems and treatment plans and engage in active and sustained collaborative treatment and progress monitoring [63]. The secure server and website aim to support communication with providers by delivering automated email alerts to enrolled providers when additional clinical support may be needed.

The LiveWell technology was supported by coaches with bachelor’s degrees who did not have professional mental health training. The coaches were trained and supervised for their roles. Details of the coach training and supervision are presented elsewhere [63]. The coach supports app use adherence, self-management, and clinical care communication (Figure 6). The coach uses a supportive accountability model to facilitate app use by working with the user to establish a bond, legitimacy, and accountability [63,135]. The coach provides self-management support using a simplified adaptation of motivational interviewing, which is effective with brief consultations administered by individuals without professional mental health training [63]. The coach also uses a chronic disease self-management model to provide app content guidance that assists the user by setting appropriate target goals, personalizing a Wellness Plan, monitoring target progress, and enacting and adjusting plans based on success or problems [63,86-92,125]. There is a clear division of labor between the technology and the coach to ensure the coach operates within the scope of nonclinical practice. The technology operates as a psychotherapeutic strategy expert and provides status summaries and alerts to the coach, who uses flow sheets and structured scripts to serve as a technology use concierge [63]. In addition, the coach works to support communication and collaboration with the care provider. The coach is prompted via server email alerts to contact providers via telephone when user self-assessments indicate problems with treatment adherence or the presence of early warning signs, worsening, or severe symptoms.

Coaching starts with a structured face-to-face meeting that addresses how using self-management strategies within the app can assist users in managing their wellness (Multimedia Appendix 4). The coach works with the user to review their experiences with normal ups and downs, early warning signs and symptoms, episodes, and related crises. This review leads to developing a personalized 9-point wellness rating scale to facilitate the self-monitoring of signs and symptoms. Next, the coach walks the user through the app and has the user complete a Daily Check-In and Daily Review. The user then sets specific goals for medication adherence, sleep duration, routine bedtime and risetime, and wellness rating range. The coach encourages the user to set parameters known to facilitate health, including maintaining medication adherence, adequate sleep duration, regular bed and wake windows, and “balanced” wellness ratings (expected ups and downs due to routine events) [5,18,26,33,97,98]. The coach wraps up the face-to-face meeting clarifying the coach’s role and obtaining a commitment to app use and target goal achievement.

Following the face-to-face meeting, 6 scheduled coaching calls occur during weeks 1-4, 6, and 16 (Figure 6). Before each call, the coach reviews a dashboard summarizing app use and the percentage of days that personalized target goals were met [64]. At each call, the coach uses the summary and a structured script to review progress and guide app use (Multimedia Appendix 4). To provide closure and a time-limited treatment, the sixth and final call wraps up working with the coach as well as the request to check-in daily [143]. The coach reviews with the user what they learned and what future plans may assist the user in living well. The user is encouraged to commit to using the strategies they have found helpful and return to app use as needed. The user is asked if they would like to continue to receive daily notifications on their smartphone as a reminder to check-in (Figure 6). The user is also asked to continue carrying their smartphone whenever they leave home and to wear a Pebble watch all day, every day, to allow ongoing behavioral monitoring for study purposes.

**Figure 6 figure6:**
[figure not shown]
Study timeline.

All coach face-to-face meetings and telephone calls were audiotaped. To assess coach fidelity, 15% of the completed coach face-to-face meetings and 15% of the weekly scheduled call audiotapes were randomly selected for review each month. Coach fidelity was then assessed using an adapted version (Multimedia Appendix 4) of the behavior change counseling index [144] scored by a trained mental health professional (psychologist). Exit questionnaires assessing smartphone app usability and coaching support were delivered at study week 48 through a web survey sent by the coaches to all participants in the intervention arm (Multimedia Appendix 5). In addition, exit interviews were completed by telephone after week 48 for the first 15% of participants exiting the intervention arm (Multimedia Appendix 5). These exit questionnaires and interviews were completed to obtain user feedback on the intervention to assist with the ongoing development of LiveWell [65].

### Intervention Evaluation

#### Overview

An RCT to evaluate LiveWell has been carried out, and data analysis is underway for the following: aim (1) to establish the capacity of LiveWell to reduce relapse and symptom burden and improve QOL in bipolar disorder, aim (2) to investigate the impact of LiveWell on proximal behavioral targets and the relationship between changes in these targets and changes in relapse rate and symptom burden, and aim (3) to identify novel behavioral signatures in individuals with bipolar disorder that predict treatment response and relapse. Aim 1 will test the following hypotheses: primary hypothesis—participants in the intervention group will experience (H1) a longer time to relapse relative to treatment as usual (TAU); secondary hypotheses—participants in the intervention group will experience (H2) a lower percentage of time being symptomatic, (H3) lower symptom severity, and (H4) a better QOL relative to TAU. Aim 2 will test the following additional hypotheses: primary hypothesis—participants in the intervention group will experience (H1) larger improvements in proximal behavioral targets (eg, medication adherence) relative to TAU; secondary hypotheses—variation in the proximal behavioral targets will account for substantial variance in the (H2) primary clinical outcome (time to relapse) and secondary clinical outcomes of (H3) percentage time symptomatic and (H4) symptom severity; proximal behavioral targets will mediate the intervention effect on the (H5) primary clinical outcome (time to relapse) and the secondary clinical outcomes of (H6) percentage time symptomatic and (H7) symptom severity; tertiary hypotheses—participants in the intervention group will experience (H8) an increase in performance determinant scores for each target, and at the final time point, will have (H9) higher performance determinant scores for each target relative to TAU. Aim 3 is exploratory and will develop a database of behavioral sensing (intervention and TAU arms) as well as app use and self-assessment (intervention arm only) data. The relationships between these data and clinical status assessment data will be examined with the long-term goal of better predicting current relapse risk, treatment response, and longitudinal course for individuals with bipolar disorder.

#### Entry Criteria

To facilitate recruitment of eligible participants and minimize exclusions while maximizing safety and study power, the following inclusion and exclusion criteria were used: The inclusion criteria were as follows: (1) adults aged 18 to 65 years, (2) individuals with bipolar disorder type I, and (3) a minimum of one acute episode in the last 2 years. Exclusion criteria were as follows: (1) not receiving psychiatric care, (2) current mood episode, (3) current severe suicidal ideation or a recent serious suicide attempt (last 3 months), (4) current substance use disorder (last 3 months), (5) visual impairments limiting mobile phone use, and (6) inability to speak and read English.

#### Ethics Approval

The study was reviewed and approved by the Northwestern University Institutional Review Board (STU00202860).

#### Recruitment, Screening, and Enrollment

The RCT for LiveWell recruited participants from the Chicago and Minneapolis-Saint Paul areas. At both sites, recruitment letters were sent to eligible individuals (bipolar disorder diagnosis, 18-65 years, and consent to contact for research) whose information was available in site-specific research registries or electronic health record data warehouses. The recruitment letters were followed up with phone calls from the study staff. Study recruitment information was also available for both sites at ClinicalTrials.gov, ResearchMatch.org, and WeSearchTogether.org websites. In the Chicago area, individuals were also recruited via mental health and university clinic presentations, flyers, brochures, e-mails to mental-health providers affiliated with Northwestern Medicine, and advertisements (Facebook, Reddit, Craigslist, Google AdWords, Chicago Transit Authority, digital, and print newspapers).

The study team contacted individuals via telephone (research registries) or individuals contacted the study team on the web, by email, or telephone. Individuals then completed a web based or telephone screening consent and completed a brief web-based or telephone-based eligibility screener (Multimedia Appendix 6). Eligible individuals were scheduled for telephone screening using a modified Mini International Neuropsychiatric Interview [145-147] and the National Institute on Drug Abuse Quick Screen followed by the Alcohol Use Disorders Identification Test and National Institute on Drug Abuse-modified assist for additional substance use disorders screening. A suicide attempt screener was also delivered, and demographic information was obtained. If still eligible, individuals attended a face-to-face clinic visit at which written consent was completed, followed by a structured interview with a trained mental health clinician (psychiatrist or psychologist) using an abbreviated and modified version of the Affective Disorders Evaluation and Clinical Monitoring Form [148-150]. Individuals with a confirmed diagnosis at the clinic visit were scheduled for a baseline telephone assessment and enrolled if no exclusion criteria were present at this assessment. Individuals who exhibited a current mood episode or substance use disorder, severe suicidality, or a recent serious suicide attempt at any step during screening were offered the opportunity to repeat the step at a later date and continue the screening process if the exclusion criteria were resolved (Multimedia Appendix 6).

At their initial face-to-face coaching meeting, intervention arm participants were asked if they wanted to allow any of their mental health providers to access a secure password-protected website that summarizes their self-report data (Daily and Weekly Check-Ins). If a participant consented to provider participation, a letter offering participation was mailed to the provider, and the coach contacted the provider by telephone. Providers interested in participating completed a web-based, verbal, or written consent form before receiving access to the website. Providers could opt to receive alerts via email or telephone when participant self-report data indicated reduced medication adherence, increased or decreased sleep duration, or deterioration in their daily wellness ratings. Providers were not required to opt for alerts to participate in the study. To allow access to the widest range of participants, participants were not required to allow any providers to access the website and providers were not required to consent to access the website or receive alerts for a participant to enroll in the study. However, as part of the written consent to participate in the study, all participants agreed to allow their psychiatrist to be contacted in the event of self-rated crisis situations, including daily wellness ratings of +4 or −4, new onset of depression (PHQ-8 score≥10), new onset of mania (ASRM score≥6), or other indications of emergent clinical problems or mental health deterioration.

#### Randomization

A biostatistician, blinded to screening and baseline assessment data, conducted computer-generated randomization on a 2:3 ratio (control:intervention) stratified based on clinical status (low risk—asymptomatic recovery; high risk—continued symptomatic, recovering, prodromal, and symptomatic recovery; Tables 4 and 5). Patients were randomized in permuted blocks of 5 at each site. The unbalanced design increases power to investigate effects within the intervention arm with minimal effect on the investigation of outcomes. Participants were stratified because time to relapse is likely to be significantly shorter for the high-risk participants who have not met the time or symptom number criteria for recovery from the last episode or who are recovered but have subsyndromal or prodromal symptoms [9,94,151,152]. Although many prior face-to-face psychotherapy studies restrict participant inclusion to those in asymptomatic recovery [10-15,18], this study includes additional high-risk individuals to increase access to the intervention.

**Table 4 table4:** Clinical status when in an episode.

DSM 4 episode criteria	Episode entry criteria^a^ met?	Number of moderate symptoms of	Impairment	Consecutive days	PSR^b^
Mania	Yes	Mania≥3 if elevated Mania≥4 if only irritable	≥Moderate or hospitalized or psychosis	≥7 or hospitalized	5-6
Depression	Yes	Depression≥5	≥Moderate	≥10 out of 14	5-6
Mixed^c^	Yes, for both mania and depression	Criteria for both mania and depression	≥Moderate	≥7	5-6
Hypomania	Yes	Mania≥3 if elevated Mania≥4 if only irritable	< Moderate and not hospitalized and no psychosis	≥4	3

^a^Entry criteria: mania—moderate severity elevated, expansive, or irritable mood ≥ 7 consecutive days; depression—moderate severity depressed mood or loss of interest/pleasure ≥ 10 out of 14 consecutive days; hypomania—moderate severity elevated, expansive, or irritable mood ≥ 4 consecutive days and < 7 consecutive days. Clinical Monitoring Form symptom severity scale: none=0, mild=0.5, moderate=1, marked=1.5, and severe=2.

^b^PSR: Psychiatric Status Rating score.

^c^Mania with concurrent depression for 1 week. Count depressive symptoms for 5/7 consecutive days instead of 10/14.

**Table 5 table5:** Clinical status when not in an episode.

Clinical Monitoring Form criteria	Recovered from last acute episode?	Symptom count^a^ and impairment	PSR^b^
Continued symptomatic	No	Symptom count>2 or ≥ moderate impairment	3-4
Prodromal	Yes	Symptom count>2 or new^c^ or ≥ moderate impairment	2-4
Recovering	No, recovering ≤8 consecutive weeks	Symptom count≤2 and < moderate impairment	1-2
Symptomatic recovery	Yes	Symptom count>0 and ≤2 and < moderate impairment	2
Asymptomatic recovery	Yes	Symptom count=0 and < moderate impairment	<2

^a^Symptom count: sum of symptom severity, if |severity| ≥1 round up, otherwise 0. Clinical Monitoring Form symptom severity scale: none=0, mild=0.5, moderate=1, marked=1.5, and severe=2.

^b^PSR: Psychiatric Status Rating score.

^c^Two new moderate, marked, or severe symptoms developed while in recovery.

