#### Analysis Overview

As the randomization was stratified by risk group, analyses will examine if an interaction between risk strata and the study arm is present. If no evidence of an interaction is evident, the models will be stratified or adjusted for risk strata. For time to relapse, missing data for participants who dropped out or were lost to follow-up will be censored at their last study visit. Percentage time symptomatic will be calculated based only on the observed time in the study. For longitudinal data (symptom severity, QOL, targets), multiple imputation using Markov Chain Monte Carlo methods will be used to address missing data by creating five unique data sets (SAS procedure PROC MI), and the results will be combined (SAS procedure PROC MIANALYZE) to obtain valid statistical inferences and least square means of the outcomes for each time point data will be calculated.

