#### Aim 1: Primary and Secondary Outcomes Analysis

Time-to-relapse curves will be constructed using the Kaplan-Meier method. Log-rank tests will be used to determine if there is a univariate impact of the study arm while adjusting for risk strata. Cox proportional hazard models will then be fit to adjust for risk strata. Proportional hazards assumptions will be assessed, and the estimated hazard ratio and CIs will be presented. To compare percent time symptomatic, linear regression models will be used to determine if there was an interaction between risk strata and the study arm. If no evidence of interaction is seen, the main effect of arm will be reported and least square means will be estimated while adjusting for risk strata. Generalized linear mixed models for longitudinal data will be used for symptom severity and QOL measures. We will examine the interactive effects of the intervention on time. If no interaction is detected, we will test the independent effects of time as well as the treatment group.

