#### Aim 2: Target Analysis

Generalized linear mixed models will be used to examine the effects of time, risk strata, and study arm on longitudinal target and determinant data. We will use the framework of Muller et al [200] to identify the targets that mediate the effect of the intervention on time to relapse, percentage time symptomatic, and symptom severity. To compare the performance determinant scores for each target at the final time point, *t* tests with correction for multiple testing between the two groups will be used.

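### Randomization was blocked by site as well as stratified by risk, but the stated models adjust for risk only and the tertiary week-48 determinant t tests adjust for neither

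*Protocol article*

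**What the plan says.** The Randomization section describes two restrictions on allocation. It was "stratified based on clinical status (low risk—asymptomatic recovery; high risk—continued symptomatic, recovering, prodromal, and symptomatic recovery; Tables 4 and 5"), and "Patients were randomized in permuted blocks of 5 at each site". The recruitment section names two areas: "The RCT for LiveWell recruited participants from the Chicago and Minneapolis-Saint Paul areas".

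The Analysis Overview says that risk is examined because randomization was stratified by risk group, and sets this rule: "If no evidence of an interaction is evident, the models will be stratified or adjusted for risk strata".

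The specific analyses follow it:
- Primary outcome, test: "Log-rank tests will be used to determine if there is a univariate impact of the study arm while adjusting for risk strata".
- Primary outcome, model: "Cox proportional hazard models will then be fit to adjust for risk strata".
- Percentage of time symptomatic: linear regression, with least square means adjusted for risk strata.
- Symptom severity and quality of life: mixed models with no covariate named in the Aim 1 section, so the general risk rule covers them.
- Targets and determinants over time (Aim 2): mixed models with time, risk strata and arm.
- Determinant scores at the final time point (H9, tertiary): t "tests with correction for multiple testing between the two groups will be used".

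No analysis section mentions site.

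**The concern.** When allocation is balanced within levels of a factor that affects the outcome, the true sampling variance of the treatment comparison falls. An analysis that leaves the factor out does not see this. It keeps the factor's variation in its residual, so its standard error is too large, its actual type I error falls below the nominal level, and it gives up power.

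The article accepts this reasoning for risk but applies it to only one of the two restrictions it describes. For H9 it fixes a test that uses neither. H9 also has no baseline score to lean on: the Determinant Assessments section gives the control arm the questionnaires only at week 48. Risk and site are therefore natural covariates, known for everyone.

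What is at stake is efficiency and consistency between design and analysis. There is no false-positive risk.

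**Working it through.** **1. The plan's own figures (Sample Size Considerations).** Inputs: 200 participants, 2:3 allocation, control relapse 0.60, hazard ratio 0.61, 12% loss, 30 months of accrual plus 12 months of follow-up, 5% type I error taken as two-sided.
- Relapse in the intervention arm under proportional hazards: 1 − 0.40^0.61 = 0.428, stated as 43%.
- Exponential relapse, 12% yearly loss and uniform accrual, with follow-up running to 12 months after accrual ends, give about 136 events. Power = Φ(√(135.6 × 0.4 × 0.6) × |ln 0.61| − 1.96) = Φ(2.820 − 1.960) = 0.805.
- Secondary outcome, 176 evaluable (70.4 and 105.6): detectable effect = 2.80 × √(1/70.4 + 1/105.6) = 0.431, stated as 0.43.

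Both reproduce, and neither depends on site.

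**2. Formula for a linear model.** If an omitted, balanced factor explains a share R² of outcome variance, the model standard error is too large by the factor 1/√(1 − R²). The actual two-sided type I error is 2 × (1 − Φ(1.96/√(1 − R²))).

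| R² of site (assumed) | SE too large by | Actual type I error | Site difference, two equal sites |
|---|---|---|---|
| 2% | 1.0% | 4.8% | 0.29 SD |
| 5% | 2.6% | 4.4% | 0.46 SD |
| 10% | 5.4% | 3.9% | 0.67 SD |

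The last column is 2 × √(R²/(1 − R²)).

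**3. Simulated trials, continuous outcome.** Assumptions: two sites and two risk groups, each split equally; blocks of 5 (2:3) within each site-by-risk cell; 176 evaluable; nominal 5% test with no multiplicity correction; power at the plan's effect size of 0.43. There were 6,000 trials for type I error (simulation error about 0.003) and 4,000 for power (about 0.007). All three analyses were run on the same data. Entries are unadjusted t / risk / risk and site.

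| Site effect | Risk effect | Type I error | Power |
|---|---|---|---|
| 0.2 SD | 0.5 SD | 0.043 / 0.050 / 0.050 | 0.77 / 0.79 / 0.79 |
| 0.5 SD | 0.5 SD | 0.039 / 0.045 / 0.051 | 0.75 / 0.77 / 0.79 |
| 0.8 SD | 0.5 SD | 0.032 / 0.036 / 0.050 | 0.73 / 0.74 / 0.78 |
| 0.5 SD | 1.0 SD | 0.024 / 0.042 / 0.048 | 0.69 / 0.77 / 0.79 |

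Cross-check at site 0.5 SD, risk 0.5 SD: the formula predicts that leaving out site inflates the SE by √(1 + 0.5²/4) = 1.031. The mean model SEs were 0.1583 without site and 0.1536 with it, a ratio of 1.031.

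Power lost by adjusting for risk only: 0.2 points (site 0.2 SD), 1.7 to 2.0 points (0.5 SD) and 4.4 points (0.8 SD). Power lost by the unadjusted t test, in table order: 2.2, 3.3, 5.8 and 10.0 points.

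**4. Simulated trials, log-rank test.** 200 participants, 12-month follow-up, assumed risk hazard ratio 2. Entries are unstratified / risk / risk and site.

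| Site hazard ratio | Type I error | Power |
|---|---|---|
| 1.25 | 0.041 / 0.049 / 0.052 | 0.66 / 0.69 / 0.69 |
| 1.5 | 0.040 / 0.047 / 0.049 | 0.65 / 0.67 / 0.68 |
| 2 | 0.036 / 0.042 / 0.050 | 0.63 / 0.65 / 0.67 |

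Only the differences within a row matter here. The level of power reflects the 12-month follow-up used in this simulation. The planned risk-stratified test loses 0 to 2 points by leaving out site.

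**The case against.** The case for leaving the plan alone is substantial.

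- Risk is the only factor the article calls a stratification factor and the only one it gives a prognostic reason for, and the models do use it. A reader might infer that the trial's error bars ignore the design. The text does not support that: only site is missing from the models, and only H9 lacks both factors.
- The error is on the safe side. The tests remain valid.
- No site effect is documented, and the upper assumptions are generous: R² of 5% or 10% implies a site difference larger than the 0.43 SD treatment effect the trial was sized for. A reader might also infer that the sites recruited through wholly different channels. In fact both used letters to registry and health-record patients, follow-up calls and the same three websites; "In the Chicago area, individuals were also recruited via mental health and university clinic presentations, flyers, brochures" and advertisements were additions. Entry criteria were common, and outcomes were assessed by telephone by blinded assessors.
- For H9, the article expects risk to shorten time to relapse. It says nothing about risk and determinant scores. The 10-point loss needs an assumed 1.0 SD risk effect as well as a 0.5 SD site effect, and H9 is tertiary.
- A reader might add that the trial is already short of power. The stated 80% reproduces from the stated inputs. Whether those inputs fit the planned follow-up is a separate question that does not bear on site.
- In the Cox model, omitting a prognostic factor draws the hazard ratio toward 1. This is the difference between a marginal and a conditional hazard ratio, not a faulty test, and nothing in the article allows it to be sized.
- A condensed article may leave the covariate list to the analysis plan.

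These objections limit the size of the point. They do not remove it: the article states an adjustment rule, grounds it in the randomization, and applies it to one of the two restrictions it reports. For H9 it names a specific test outside that rule.

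**Conclusion.** The mismatch between randomization and analysis is real and small. The planned analyses remain valid and slightly conservative. The risk-adjusted analyses, including the primary test, lose about 0 to 2 points of power for site effects up to 0.5 SD or a hazard ratio of 2; the linear analysis loses about 4 points at 0.8 SD. The unadjusted H9 t tests lose about 2 to 10 points, but only if risk and site affect determinant scores.

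All sizes rest on assumed effects and on sites and risk groups of equal size. They also assume that blocks were formed within each site-by-risk cell, which is the natural reading of the Randomization section but is not stated outright.

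**What to change.** - Stratify the log-rank test and the Cox model by risk and site (four strata).
- Add site as a fixed effect to the percentage-time regression and to all mixed models.
- Replace the H9 t tests with linear regression of the week-48 score on arm, risk and site, keeping the multiplicity correction.
- State whether the blocks of 5 were formed within each site-by-risk cell.

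With two sites, the statistical cost is one degree of freedom in the linear and mixed models. In the simulations the four-stratum log-rank test was never less powerful than the two-stratum test.

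The procedural cost is larger than a change of wording. The article reports that follow-up ended in April 2020 and that analysis is underway. The change should therefore be dated and documented before results by arm are seen. If that is no longer possible, keep the stated analyses as planned and report the site-adjusted ones as labelled sensitivity analyses.
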